### Quality control data collection

To maintain the high quality of this trial and ensure its adherence to the protocol, all investigators and drug administrators participating in the research will be trained rigorously based on a standardized operation practice (SOP) manual. Withdrawals or dropped visits will also need to be explained on case report forms (CRFs). All data will be documented on a standardized CRF and instantly recorded in the database via the ClinResearch Electronic Data Capture System (http://www.tcmcec.net/crivrs/). The monitor will review the CRFs, check the inclusion, exclusion and withdrawal criteria, as well as ensure information on the CRFs is in accordance with those in the source medical records. Original CRFs will be reserved at the research center for 5 years after completion of the study. The validity and authenticity of the multicenter trial will be guaranteed by establishing three committees, including the clinical trial guidance committee, the data and safety monitoring board and the outcome evaluation committee, each respectively being responsible for the trial design and executing the process, monitoring the data collection process to control its quality and evaluating the outcomes. The flow diagram of enrollment, interventions and assessments is shown in Fig. 1.

### Sample size

The sample size was estimated according to the relevant data from the losartan study published in *New England Journal of Medicine* [32, 33]. These results showed that the proportion of patients with the ACR reduced by 50% or more in the losartan group was 12.5% and the preliminary study of TSF data manifested that TSF as an add-on study can improve 50% of patients. The estimated proportion of patients with the ACR reduced by 50% or more was 18.7%. The estimated sample size formula was tested using the hypothesis of two population rates:
$$ n={\frac{\left[ u\alpha \sqrt{2p\left(1-p\right)}+ u\beta \sqrt{p1\left(1-p1\right)+p2\left(1-p2\right)}\right]}{{\left(p1-p2\right)}^2}}^2 $$

where *n* is the sample size; *p*_1_ and *p*_2_ are the sample rates, and *p* = (*p*_1_ + *p*_2_) / 2 is the sample average rate; and *α* is the type 1 error and *β* is the type 2 error, while *u*_*α*_ and *u*_*β*_ are the locus of the corresponding standard normal distribution. According to the unilateral test, *u*_*α*_ = 1.64485 and *u*_*β*_ = 0.84162, and substituting these into the formula presents *n* = 274.46. Therefore, 275 patients were needed in each group. Considering a dropout rate of no more than 15%, the final sample size was estimated to be 632 in total.

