### Statistical analysis

The statistical analysis of this study was completed by an independent statistician, and the detailed statistical analysis plan was formulated separately by a statistician before the inception of this trial and determined with the Principal Investigator. Three analysis sets will be used for assessment of this study: the intention-to-treat set (ITT), the per-protocol analysis set (PPS) and the safety analysis set (SAS). The ITT and PPS will be used to appraise the efficacy of TSF. If any given case exists missing a critical variable, the last observation used as the final results will be carried forward to the final data. The changes of urinary microalbumin–creatinine ratio, urinary microalbumin, GFR, creatinine and baseline information will be present after treatment. A paired *t* test or the Wilcoxon signed-rank test will be employed to compare each group. Changes relative to baseline after treatment will be compared between groups using the *t* test or the Wilcoxon rank-sum test. *P* < 0.05 will be deemed to show a statistically significant difference.

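### The trial is sized for a one-sided 5% test but analysed at an undirected P < 0.05; read two-sided, the plan's own n gives about 70% power at 275 per group, not 80%

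*Protocol article*

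**What the plan says.** Two sections of the protocol article bear on this.

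- **Sample size.** The calculation compares two proportions and is made "According to the unilateral test", with u_α and u_β given as "1.64485 and *u*_*β*_ = 0.84162". The control rate is taken from a losartan study, where the proportion "in the losartan group was 12.5"%. For the TSF arm, "The estimated proportion of patients with the ACR reduced by 50% or more was 18.7"%. The result is n = 274.46, so "275 patients were needed in each group". After an allowance for 15% dropout, "the final sample size was estimated to be 632 in total".
- **Statistical analysis.** Changes from baseline are compared between groups by a t test or a Wilcoxon rank-sum test, and within groups by the paired equivalents. One threshold serves for all of them: P < 0.05 "will be deemed to show a statistically significant difference". No direction is given.

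The same section refers to a separate statistical analysis plan, which is not available here.

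**The concern.** The value 1.64485 is the 95th percentile of the standard normal distribution. It is the critical value of a one-sided 5% test, or of a two-sided 10% test. A P < 0.05 rule for a difference, with no direction named, is by convention two-sided and corresponds to 1.95996. The two sections therefore do not describe the same test unless the reader assumes that the one-sided choice carries over.

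What is at stake is the call on the primary result. A result in favour of TSF with a two-sided P between 0.05 and 0.10 would be positive by the threshold in the Sample size section and negative by the usual reading of the Statistical analysis section. Neither way of settling it leaves the plan as it stands: one gives less than the planned 80% power, the other a false-benefit rate of 5%.

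**Working it through.** **Inputs, all from the Sample size section unless noted.** p1 = 0.125, p2 = 0.187, u_α = 1.64485, u_β = 0.84162, stated n = 274.46 (275 per group), total 632. With 1:1 allocation (Randomization and concealment section), 632 / 2 = 316 per group. The two-sided 5% critical value is 1.95996.

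**Step 1. The plan's own figure.** The printed formula, with the square applied to the numerator bracket (the standard reading), is

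n = [u_α √(2p(1−p)) + u_β √(p1(1−p1) + p2(1−p2))]² / (p1−p2)²

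- p = (0.125 + 0.187) / 2 = 0.156
- √(2 × 0.156 × 0.844) = 0.51316
- √(0.109375 + 0.152031) = 0.51128
- numerator: (1.64485 × 0.51316 + 0.84162 × 0.51128)² = (0.84406 + 0.43030)² = 1.6240
- denominator: 0.062² = 0.003844
- n = 422.5

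The stated 274.46 is not reproduced. That is a separate defect. To keep it apart from sidedness, the effect of sidedness is worked out below on both bases.

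**Step 2. Sidedness alone, taking 274.46 as a valid one-sided n for 80% power.**

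- Two-sided power at 275 per group: Φ(0.84162 + 1.64485 − 1.95996) = Φ(0.5265) = 0.70.
- Two-sided power at 316 per group: Φ(2.48647 × √(316 / 274.46) − 1.95996) = Φ(0.708) = 0.76.
- n per group for 80% two-sided: 274.46 × [(1.95996 + 0.84162) / (1.64485 + 0.84162)]² = 274.46 × 1.2695 = 348.4, so 349.

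**Step 3. Sidedness on the stated rates.** Power = Φ{[√n × 0.062 − u_α × 0.51316] / 0.51128}.

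| n per group | one-sided 5% | two-sided 5% | loss from sidedness |
|---|---|---|---|
| 275 | Φ(0.360) = 64.1% | Φ(0.044) = 51.7% | 12.4 points |
| 316 | Φ(0.505) = 69.3% | Φ(0.188) = 57.5% | 11.8 points |

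The formula's requirement on these rates is 422.5 per group one-sided and, with 1.95996, (1.00576 + 0.43030)² / 0.003844 = 536.5 two-sided. The gap between 80% and 64% at 275 per group comes from Step 1, not from sidedness.

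**Step 4. The other branch.** If the analysis is one-sided at 5%, the probability of a false claim in favour of TSF is 5%. A two-sided 5% test allows 5% / 2 = 2.5% in that direction.

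**The case against.** The best reply is that the Statistical analysis section never says two-sided. A one-sided 5% sizing and a P < 0.05 rule can both be true of one design, the Sample size section does fix an alpha, and the separate analysis plan may well state the direction. This stands in part. A reader might infer that the document contradicts itself outright or leaves alpha undefined. It does neither: the inconsistency rests on the convention that an unlabelled P value is two-sided.

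It does not dispose of the point, because this is more than an omitted detail. The article commits to a one-sided sizing and then states an undirected threshold, which it also applies to the within-group tests and to GFR and creatinine. The Abstract expects benefit from TSF, but an expected direction is not a reason for a one-sided 5% test. If the unseen plan is two-sided, the sizing needs correcting. If it is one-sided, the Statistical analysis section should say so and the choice needs a justification.

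A second reply is that 275 per group is the least favourable of the plan's two sample sizes, since an ITT analysis with last observation carried forward could include all 316. That is fair, and both are shown. The figures at 316 are best regarded as upper bounds, because carried-forward values may dilute the effect.

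A third is that none of these powers is that of the primary test. That is also right. The Primary outcomes section specifies change in ACR, the sizing uses a responder proportion, and the article gives no standard deviation from which the power of the t or Wilcoxon test could be found.

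**Conclusion.** The point holds in a bounded form. The sizing uses a one-sided 5% critical value, the analysis states an undirected P < 0.05, and nothing in the article reconciles or justifies the difference.

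- **Read two-sided:** on the plan's own n, power falls from 80% to about 70% at 275 per group, or to about 76% at 316. On the stated rates, sidedness costs about 12 points at either size.
- **Read one-sided:** the error rate in favour of TSF is 5% rather than 2.5%.

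Two stronger readings are tempting and not supported. One is that sidedness brings power down to 52%: that figure also contains the failure to reproduce 274.46, and only about 12 points of the fall are due to sidedness. The other is that the primary analysis has 52% or 70% power: these figures apply only to the proportion with ACR reduced by 50% or more, and the power of the ACR-change test cannot be computed from the article at either alpha.

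The conclusion assumes the conventional two-sided reading of an undirected P value, the standard reading of the printed formula and, for the 70% and 76%, acceptance of 274.46.

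**What to change.** Before unblinding, state in both the Sample size and the Statistical analysis sections that the primary comparison is two-sided at 0.05 (equivalently one-sided 0.025) and will be reported with a 95% confidence interval. Make sure that the separate analysis plan says the same. Restate the power at the planned size with 1.95996 in place of 1.64485, and label it as power for the responder endpoint.

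The cost is about a sentence in each section and a recalculated power. The downside is that the stated power falls below 80%. The enrolment target stays as it is. Restoring 80% two-sided power would need more patients (about 349 per group before dropout on the plan's own n, 537 on the stated rates); that is a separate decision, and this fix does not depend on it. At manuscript submission 95 patients had been recruited and recruitment was continuing, so at that point the rule could still be settled before results were seen.

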**Methods/design:**

This trial is a 13-center, randomized, double-blind, placebo-controlled study. A total of 632 participants will be randomized in a 1:1 ratio to an experiment group (TSF plus losartan) and a control group (placebo plus losartan). The trial cycle will last 24 weeks. The primary outcome will be the change in the urine microalbumin–creatinine ratio from baseline to week 24. The secondary outcome will be the change in the rate of progression to the clinical proteinuria period after intervention, the rate of urine microalbumin negative conversion, the rate of normal urinary microalbumin, the doubling rate of the baseline creatinine value and the glomerular filtration rate between the two groups. Safety in medication will also be evaluated.

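### The printed sample size formula gives 423 per group, not 275, so 632 patients give about 63–69% power for the stated effect instead of 80%

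*Protocol article*

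**What the plan says.** The Sample size section bases the trial on a responder proportion. For control it states that "the proportion of patients with the ACR reduced by 50% or more in the losartan group was 12.5" per cent. For TSF as an add-on it assumes a relative improvement of one half: "The estimated proportion of patients with the ACR reduced by 50% or more was 18.7" per cent.

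The method is the usual normal-approximation formula for two independent proportions, with a pooled variance under the null. The test is one-sided ("According to the unilateral test"), with normal quantiles 1.64485 and 0.84162, that is, α = 0.05 and 80% power. The section reports n = 274.46 and concludes: "Therefore, 275 patients were needed in each group".

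The last step is: "Considering a dropout rate of no more than 15%, the final sample size was estimated to be 632 in total". The Abstract repeats the total: "A total of 632 participants will be randomized in a 1:1 ratio".

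**The concern.** The section prints every input, the formula and the answer, and the answer does not follow. A difference of 6.2 percentage points between rates of this size needs well over 400 patients per group for 80% power at one-sided 5%. The stated figure is about a third too small.

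This calculation is the only support the article gives for 632. A reader will take the trial to have a four-in-five chance of detecting the stated effect. If the true chance is nearer two in three, a null result would be read as stronger evidence against TSF than the design can supply.

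**Working it through.** **Inputs** (all from the Sample size section): p1 = 0.125; p2 = 0.187; p = (0.125 + 0.187)/2 = 0.156; u_α = 1.64485; u_β = 0.84162; dropout 15%; 632 in total, 316 per group.

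**Formula as printed**, with the square read as applying to the bracket in the numerator (the typeset exponent is misplaced, but taking it literally gives about 109,906):

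n = [u_α √(2p(1−p)) + u_β √(p1(1−p1) + p2(1−p2))]² / (p1−p2)²

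**1. Evaluate it.**
- √(2 × 0.156 × 0.844) = √0.263328 = 0.51315; × 1.64485 = 0.84406
- √(0.109375 + 0.152031) = √0.261406 = 0.51128; × 0.84162 = 0.43030
- Sum 1.27437; squared 1.62401
- Divided by 0.062² = 0.003844: n = 422.5, so **423 per group**

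**2. Reproduce the plan's 274.46.** Leave out the factor 2 under the first root only:
- √(0.156 × 0.844) = √0.131664 = 0.36286; × 1.64485 = 0.59684
- 0.59684 + 0.43030 = 1.02715; squared 1.05503; divided by 0.003844 = **274.46**

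This matches to two decimals. It identifies the slip and confirms that 0.125 and 0.187 were the rates used.

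**3. Rule out other explanations** (80% power, per group).

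| Variant | n |
|---|---|
| p2 = 18.75% (12.5% × 1.5, unrounded) | 416.3 → 417 |
| Unpooled variance | 420.4 → 421 |
| Arcsine | 419.7 → 420 |
| Continuity-corrected | 455 |
| Two-sided 5% | 536.5 → 537 |

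None comes near 275. With the correct formula, 274.46 would need a TSF rate of about 20.35%.

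**4. Power for 12.5% against 18.7%.** Power = Φ{[√n × 0.062 − u_α × 0.51315] / 0.51128}.

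| Per group | Situation | One-sided 5% | Two-sided 5% |
|---|---|---|---|
| 268 | 632 less 15% (632 × 0.85/2 = 268.6) | 63.1% | 50.7% |
| 275 | the stated requirement | 64.1% | 51.7% |
| 316 | all randomised patients analysed | 69.3% | 57.5% |
| 423 | corrected requirement | 80.0% | 70.1% |

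The two-sided column matters because the Statistical analysis section gives only P < 0.05 and does not say that the test is one-sided.

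With 268 per group, 80% one-sided power needs a TSF rate of about 20.5%. That is a relative gain of 64% (0.2045/0.125 = 1.64), not 50%.

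**5. Dropout step.**
- Plan: 275 × 1.15 = 316.25, taken as 316; × 2 = 632.
- To keep 275 after 15% loss: 275/0.85 = 323.5, so 324 per group, 648 in total.
- With 632 randomised, 275 per group remain only if loss is at most 1 − 550/632 = 13.0%.
- Applied to the corrected figure: 423/0.85 = 497.6, so 498 per group, **996 in total**.

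**The case against.** The strongest objection concerns scope. The responder proportion is not a listed outcome. The Primary outcomes section names the change in ACR, and the Statistical analysis section tests it with a t test or rank-sum test. The article gives neither a standard deviation nor a target difference for that analysis, so its power cannot be computed and may well exceed 63%. This stands: the 63–69% applies to the responder contrast only. It does not rescue the section, because the responder calculation is the only justification offered for 632.

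Second, 63% is the low end of the one-sided range. It assumes the full 15% loss and an analysis of completers. The plan carries the last observation forward, and ACR is measured every four weeks, so many patients who drop out would stay in the ITT analysis. With all 316 per group, power is 69%. This also stands, and the range is the fair statement. It still falls short of 80%.

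Third, the dropout error is small. The difference between 632 and 648 is 2.5%, and it costs about one percentage point of power (64.1% at 275, 63.1% at 268). That is correct, and the point is secondary to the formula error.

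No separate analysis plan could cure this. The section displays a calculation in full and states a wrong result for it.

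**Conclusion.** The concern holds. On its own formula and inputs the plan needs 423 per group and states 275, a shortfall of 148 per group (35%). The cause is an omitted factor 2 when the formula was evaluated.

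For 12.5% against 18.7% at one-sided 5%, 632 patients give 63% power after 15% loss and 69% if everyone is analysed. The design would therefore miss that effect in about 31–37% of trials, where the section implies 20%. If the test is two-sided, power is about 51–57%.

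These figures rest on the section's own rates and a normal approximation. They do not describe the power of the comparison of ACR change. The dropout inflation is also wrong as stated, with little effect. This must be fixed, because the sole stated basis for the trial's size is incorrect.

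**What to change.** Correct the Sample size section in one of two ways.

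1. **Restate.** Say that the formula gives 423 per group, and replace the implied 80% with the power of 632 patients for 12.5% against 18.7%: about 63% one-sided after 15% loss, 69% if all are analysed.
2. **Re-justify 632 on the declared primary outcome.** State a standard deviation and a target difference, with their source. As an illustration, assume a comparison of log-ACR at two-sided 5% and 80% power with 268 per group. The detectable log difference is (1.95996 + 0.84162) × SD × √(2/268). For a residual log-SD of 0.6, 0.8 or 1.0 this is 0.145, 0.194 or 0.242, a relative reduction in ACR of about 14%, 18% or 21%. These SDs are assumptions, since the article gives none. This calculation is also two-sided, unlike the one in the article, so the section should say which sidedness applies.

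In either case, inflate for dropout by n/(1 − 0.15).

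The cost is wording only, with a less favourable stated power. No extra patients are needed unless the sponsor wants to keep 80% power for the stated responder effect, which would take 996 randomised. The Trial status section reports 95 recruited at submission, so that choice was still open then.

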### Statistical analysis

The statistical analysis of this study was completed by an independent statistician, and the detailed statistical analysis plan was formulated separately by a statistician before the inception of this trial and determined with the Principal Investigator. Three analysis sets will be used for assessment of this study: the intention-to-treat set (ITT), the per-protocol analysis set (PPS) and the safety analysis set (SAS). The ITT and PPS will be used to appraise the efficacy of TSF. If any given case exists missing a critical variable, the last observation used as the final results will be carried forward to the final data. The changes of urinary microalbumin–creatinine ratio, urinary microalbumin, GFR, creatinine and baseline information will be present after treatment. A paired *t* test or the Wilcoxon signed-rank test will be employed to compare each group. Changes relative to baseline after treatment will be compared between groups using the *t* test or the Wilcoxon rank-sum test. *P* < 0.05 will be deemed to show a statistically significant difference.

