### Study visits and assessment

The intervention cycle will be 24 weeks, including a run-in period. After the research commences, visits will occur every 4 weeks during the study period. An overview of specific measurements and time points for data collection is presented in Table 1.

**Table 1 Tab1:** Measurement items and point of data capture

Visit project	Screening period/baseline	Visits 1–2, 4–5	Visit 3	Visit 6
Visiting time	–7 to 0 days	Medication 4, 8, 16, 20 weeks ±7 days	Medication 12 weeks ±7 days	Medication 24 weeks ±7 days
Collect basic medical history				
Sign informed consent	×			
Fill in general information	×			
Medical history and treatment history	×			
Determine inclusion and exclusion criteria	×			
Vital signs	×	×	×	×
Physical examination	×	×	×	×
Comorbidity and medication records	×	×	×	×
Monitoring and inspection				
Urine pregnancy test	×			
Glycosylated hemoglobin, blood lipids	×		×	×
Fasting blood sugar and blood pressure	×	×	×	×
Effectiveness observation				
Urinary microalbumin–creatinine ratio	×	×	×	×
Urinary microalbumin excretion rate	×	×	×	×
Serum creatinine	×	×	×	×
Glomerular rate filtration	×	×	×	×
24-h urinary microalbumin and 24-h urinary microalbumin quantification	×		×	×
Physico-chemical examination				
Routine blood test and routine urine test	×		×	×
Stool routine examination	×		×	×
Vital signs	×	×	×	×
ECG, liver and kidney function	×		×	×
Adverse event		×	×	×
Other work				
Random grouping	×			
Distribute drug and patient journal cards	×	×	×	
Recovery drugs, quantity statistics		×	×	×
Recycle patient’s diary card		×	×	×
End of study summary				×

*ECG* electrocardiogram

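### Last observation carried forward is fixed for missing values although ACR is measured every 4 weeks; it can bias the week-24 comparison in either direction

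*Protocol article*

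**What the plan says.** The abstract sets the target: "The primary outcome will be the change in the urine microalbumin–creatinine ratio from baseline to week 24". The Statistical analysis section gives the rule for missing data. It begins "If any given case exists missing a critical variable" and continues that "the last observation used as the final results will be carried forward to the final data". The same section fixes the between-group comparison: "Changes relative to baseline after treatment will be compared between groups using the *t* test or the Wilcoxon rank-sum test". Efficacy is assessed in the intention-to-treat and per-protocol sets. The article names no other way of handling missing values. It does say that a detailed analysis plan was written separately.

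Under Study visits and assessment, "visits will occur every 4 weeks during the study period". The ACR row of Table 1 is marked in every column: screening/baseline, the group headed "Medication 4, 8, 16, 20 weeks ±7 days", week 12 and week 24.

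On the amount of missing data, the Sample size section says "Considering a dropout rate of no more than 15" per cent.

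**The concern.** The rule uses a dropout's last ACR as the week-24 result and ignores the rest of that patient's 4-weekly series. This is sound only if ACR stops changing at dropout, and the plan gives reason to doubt that. Both arms receive losartan, and the sample size assumes that 12.5% of losartan patients and 18.7% of TSF patients will reach an ACR reduction of 50% or more. If ACR is still moving, a value from week 4 or 8 is not a week-24 value.

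At stake is the primary comparison. If one arm loses more patients, or loses them earlier, carrying values forward can create or enlarge a difference, or hide one. If the arms lose patients equally and TSF works, the effect is diluted. The confidence interval also treats the carried-forward values as measured week-24 values.

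**Working it through.** **Inputs from the protocol article.** ACR at weeks 0, 4, 8, 12, 16, 20 and 24 (Table 1); 15% dropout and 632 patients (Sample size). The total follows from the allowance: 2 × 275 × 1.15 = 632.5. Patients possibly affected: 0.15 × 632 = 94.8, about 95.

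**Assumptions, because the article gives no trajectory, dropout pattern or SD.** Effects act on log ACR and accrue linearly to week 24. A dropout's last value is equally likely to be from week 0, 4, 8, 12, 16 or 20. Dropout is unrelated to ACR.

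**Step 1, share of the week-24 change captured.** The mean last week is (0 + 4 + 8 + 12 + 16 + 20)/6 = 10, so a dropout carries on average 10/24 = 0.417 of the full change. With dropout fraction d, an arm shows m(d) = (1 − d) + 0.417d of its true log change:
- m(0.05) = 0.971
- m(0.15) = 0.9125
- m(0.25) = 0.854

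**Step 2, equal dropout.** A change shared by both arms cancels. For a true ratio of 0.80 and 15% in each arm: exp(0.9125 × ln 0.80) = 0.816. With no effect the result is 1.00, so there is no bias.

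**Step 3, unequal dropout (hypothetical).** Take 25% in one arm and 5% in the other, which averages to the planned 15%, and an assumed shared 30% fall (ln 0.70 = −0.357; ln 0.80 = −0.223; sum −0.580).

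| True ratio | More dropout in | Log difference | Estimated ratio |
|---|---|---|---|
| 1.00 | TSF | (0.854 − 0.971) × (−0.357) = +0.042 | 1.04 |
| 1.00 | control | −0.042 | 0.96 |
| 0.80 | TSF | 0.854 × (−0.580) − 0.971 × (−0.357) = −0.149 | 0.86 |
| 0.80 | control | 0.971 × (−0.580) − 0.854 × (−0.357) = −0.258 | 0.77 |

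**Step 4, simulation.** Settings: 316 per arm; log-scale SDs of 0.6 between patients, 0.45 within patients and 0.35 for individual slopes; control change −0.30; true effect −0.20 or 0. All of these are assumed. The comparator is an estimator that uses all visits under missing at random (MAR).

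| Dropout control/TSF | True effect | LOCF, linear trajectory | LOCF, early plateau | MAR, linear / plateau |
|---|---|---|---|---|
| 15%/15% | −0.20 | −0.183 | −0.191 | −0.201 / −0.199 |
| 8%/22% | −0.20 | −0.148 | −0.173 | −0.200 / −0.198 |
| 22%/8% | −0.20 | −0.217 | −0.208 | −0.201 / −0.200 |
| 8%/22% | 0 | +0.027 | +0.014 | +0.002 / +0.001 |
| 22%/8% | 0 | −0.027 | −0.012 | −0.001 / 0.000 |

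Over all 12 scenarios run, which include dropout related to ACR, the error was about 0.006 to 0.05 log units. In the worst (8%/22%, linear, true −0.20), coverage of the 95% interval fell to 84%.

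**Step 5, standard error.** The nominal LOCF standard error was 0.0565 to 0.0589. The actual standard error of the MAR estimator was 0.0592 to 0.0635. The gap was about 2% to 9%. With 15% dropout in each arm and linear trajectories, LOCF reported 0.0570. The same analysis with no missing values would report 0.0578, so losing data made the interval slightly narrower.

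**The case against.** The strongest objection is that the bias is conditional and may be small. That stands. It is nil with no effect and equal dropout, and with equal dropout and a real effect it is a small conservative shift. Nothing in the article points to a 25% versus 5% split: the trial is double-blind with an indistinguishable placebo. The shared 30% fall is not in the article either. Prior losartan use is allowed, so some patients may have had much of that fall before entry. The imbalance figures are illustrations, not forecasts.

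A reader might infer that the t-test standard error is miscalculated. The material does not support that. Under LOCF each patient contributes one value of their own, and the nominal standard error agrees with LOCF's own sampling error. In one simulation of 15% dropout per arm the two were 0.0571 and 0.0570. The 84% coverage arises where the estimate moved from −0.20 to −0.148, so bias largely explains it. The valid point is narrower: the interval describes the carried-forward quantity, not the week-24 effect.

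A reader might also infer that patients with no post-baseline ACR are scored as zero change. That is only a literal reading of the rule; the article neither says it nor defines the intention-to-treat set. Nor does the article's silence show that no sensitivity analysis exists, since the separate analysis plan is not at hand. LOCF itself, however, is a stated rule and not something left open. The per-protocol analysis is no remedy if it leaves out the patients with missing values.

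**Conclusion.** The concern holds in limited form. The protocol fixes a method that discards most of the 4-weekly ACR series for dropouts and can bias the week-24 contrast in either direction, so it cannot be defended as reliably conservative. Under the stated assumptions the shift runs from none, through 0.80 becoming 0.82 with equal 15% dropout, to about 4% either way under no effect in the hypothetical 25%/5% split. An early plateau in ACR roughly halves the error in most of the simulated cases. The shortfall in standard error is modest, about 2% to 9% against a valid week-24 estimator. All sizes rest on assumed trajectories, dropout patterns and SDs. The documents do not support saying that LOCF will bias this trial, or that its t test is numerically wrong. The rule should be changed because the data for a better analysis are already scheduled.

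**What to change.** - **Primary analysis:** replace LOCF with a likelihood-based repeated-measures model on ACR at weeks 4 to 24, on the log scale if skewed and adjusted for baseline, with the week-24 contrast primary. Multiple imputation using all visits is an acceptable alternative.
- **Intention-to-treat set:** keep all randomised patients, and state how those without a post-baseline ACR enter the analysis.
- **Sensitivity:** add one reference-based or delta-adjusted analysis for data not missing at random. Keep LOCF only as a further sensitivity analysis.
- **Consistency:** if the separate analysis plan already differs, reconcile it with the protocol.

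**Cost.** No new visits or measurements are needed. The new primary analysis rests on missing at random, which is why the sensitivity analysis is needed. There is some programming. Because the rule is in the protocol and recruitment was under way (95 patients at submission), an amendment to the protocol and analysis plan may be required. Allocation stays masked until the study is complete, so the change can be made blind.
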